### Pilates solo intervention

The women allocated to this group will participate in the Pilates solo protocol. The 16-week protocol will be implemented in 60-min Pilates solo classes three afternoons per week under supervision of an exercise science professional and a physiotherapist. The Pilates protocol will be divided into three stages:
*Warmup and stretching*: Including breathing, imprint and release, hip release, spinal rotation, cat stretch, hip rolls, scapula isolation, arm circles, head nods, and elevation and depression of scapulae exercises during warmup in all sessions.*Main stage*: A brief explanation of the purpose of the class will be provided, and the exercises will take place as detailed in Table 1. To increase the load during the protocol, TheraBand and toning ball exercises will be added at the 10th session; in the 20th session, the exercise in the arms will be added, and from the 24th session, the exercise of spinal rotation will be realized with weight of 1 kg. Exercises will be performed according to each patient’s ability (principle of sports training) to avoid pain (during and after exercising) and embarrassment associated with possible physical or even psychological and emotional difficulties.*Relaxation*: For this stage of the class, the patients will be invited to sit on the ball, spine stretch forward on the ball, self-stretch of cervical muscles on the ball (upper trapezius and scalene muscles), and actively mobilize the cervical spine. At the end of each class, a brief discussion will be held on the women’s perceptions regarding the objectives discussed in the beginning of class and whether they were achieved, and these data will be recorded by a third researcher to identify whether the participants enjoyed the class and felt that they achieved the objectives of the class.

**Table 1 Tab1:** Sixteen-week belly dance protocol (48 sessions) for women after breast cancer diagnosis (Florianopolis SC, Brazil, 2018)

	Session 1 Slow songs (up to 80 bpm) Medium songs (up to 120 bpm) Fast songs (up to 150 bpm)	Session 2 Slow songs (up to 80 bpm) Medium songs (up to 120 bpm) Fast songs (up to 150 bpm)	Session 3 Slow songs (up to 80 bpm) Medium songs (up to 120 bpm) Fast songs (up to 150 bpm)
1	Belly dance presentation	Belly dance presentation	Belly dance presentation
2	Loosening of hips	Loosening of hips	Pendulum and side hit
3	Pendulum and side hit	Movements and steps sequence	Pendulum and side hit with displacement
4	Pendulum and side hit with displacement	Undulations and round	Movements and steps sequence
5	Undulations and round	Undulations and round with displacement	Movements and steps sequence
6	Undulations and round with displacement	Egyptian basics and twist	Movements and steps sequence
7	Egyptian basics and twist	Shimmys and variations	Shimmys and variations
8	Displacements, rotations, and use of space	Displacements, rotations, and use of space	Movements and steps sequence
9	Study of Arabic Dabke folklore	Study of Arabic Dabke folklore	Movements and steps sequence
10	Dance pitcher	Dance pitcher	Movements and steps sequence
11	Dance tambourine	Dance tambourine	Movements and steps sequence
12	Study of Arabic Khalije folklore	Study of Arabic Khalije folklore	Movements and steps sequence
13	Dance with the veil	Dance with the veil	Movements and steps sequence
14	Study of Arabic Dabke folklore	Dance tambourine	Study of Arabic Khalije folklore
15	Dance with the veil	Movements and steps sequence	Displacements, rotations, and use of space
16	Review of all the movements	Review of all the movements	Review of all the movements

*bpm* beats per minute

### Belly dance intervention

Women allocated to this group will participate in the belly dance protocol. The 16-week protocol will be implemented in 60-min belly dance classes three afternoons per week under supervision of an exercise science professional and a physiotherapist. The classes will be divided into three stages:
*Warmup and stretching*: The beginning of the class will include songs with up to 80 beats per minute (bpm), thus identified as slow pace. The sequence of movements for this class stage will cover large movements involving specific joints, including flexion, extension, abduction, adduction, and rotation, initiated by the upper body until it reaches the lower limbs, lasting 10 min.*Main stage*: A brief explanation of the purpose of the class will be provided (i.e., the theory of dance or the specific step to be developed), followed by the practical part of the technical learning. The aim of this part will be for participants to learn the movements of the belly dance technique; to stimulate motor coordination, rhythm, and body awareness; and to improve aspects of flexibility and ROM of the upper limbs. The practice of the movements will be explored using individual, pair, or group dynamics involving movements corresponding to the rhythm of music or the rhythm stipulated for the women. The participants will have the artistic freedom to create their own pattern of movement based on the belly dance technique while respecting their own body awareness and allowing the expression of feelings. The evolution of the belly dance technique will be applied as outlined in Table 2. For this part of the classes, medium-paced music with up to 120 bpm will be used, as well as fast-paced music with up to 150 bpm. This part of the class will have an average duration of 40 min.*Relaxation*: This stage will be developed from slow-moving practices with music up to 80 bpm, usually the same songs used in the initial warmup and stretching. With heart rate normalization, this part will last 10 min. At the end of each class, a brief discussion will be held on the women’s perceptions regarding the objectives discussed in the beginning of class and whether they were achieved, and these data will be recorded by a third researcher to identify whether the participants enjoyed the class and felt that they achieved the objectives of the class.

**Table 2 Tab2:** Sixteen-week Pilates solo protocol (48 sessions) for women after breast cancer diagnosis (Florianopolis SC, Brazil, 2018)

Week	Session	Description of the activity
1	1	Explanatory session: What is Pilates, the basic principles of Joseph Pilates: breathing, centering, control, precision, fluency, and concentration. Clarify the positions: positioning of the pelvis, positioning of the rib cage, stabilization and movement of the shoulder girdle, and positioning of the head and cervical spine.
	2 and 3	Single-leg stretches, obliques (with feet flat on the floor), scissors, obliques roll, one-leg circle, side kick, preparation shoulder bridge performing simultaneously exercises of biceps with weight of 1 kg.
2	4	Single-leg stretches, obliques (with feet flat on the floor), scissors, obliques roll, one-leg circle, side kick, preparation shoulder bridge performing simultaneously exercises of biceps with weight of 1 kg, single-leg extension and roll up.
	5 and 6	Half-roll back (with over ball in the lumbar spine), roll up (pressing the magic circle with hands), single-leg stretch (with over ball between the shoulder blades), one-leg circle (with TheraBand around the thigh with both knees flexed), preparation shoulder bridge tightening the over ball between the knees and performing simultaneously exercises of biceps with weight of 1 kg, hell squeeze prone (pressing magic circle on ankles), side kick, spine twist.
3	7	Half-roll back (with over ball in the lumbar spine), roll up (pressing the magic circle with hands), single-leg stretch (with over ball between the shoulder blades), one-leg circle (with TheraBand around the thigh with both knees flexed), preparation shoulder bridge tightening the over ball between the knees and performing simultaneously exercises of biceps with weight of 1 kg, hell squeeze prone (pressing magic circle on ankles), side kick, spine twist.
	8 and 9	Half-roll back, single-leg stretches, double-leg stretches, preparation shoulder bridge (with feet on top of the ball), top-leg abduction, top-leg circles, staggered legs, both legs together.
4	10	Half-roll back, obliques (with feet on the floor, tightening the over ball, and extending the lower member to the side of the rotation of the trunk), double-leg stretch, scissors (with over ball in sacral region), preparation shoulder bridge (with feet on top of the ball), top-leg circles, both legs together.
	11 and 12	Obliques roll (with magic circle the knees), hundred (with feet on the floor), obliques (with feet on the floor and tightening the over ball between the knees, jackknife, both legs together and lateral flexion.
5	13	Obliques roll (tightening magic circle between knees), hundred (with feet on the floor), jackknife, top-leg abduction (with the lower limbs within the magic circle), top-leg circles, staggered legs (with the lower limbs within the magic circle).
	14 and 15	Roll up (with TheraBand on feet), slow double-leg stretch, double-leg stretch, preparation shoulder bridge (with feet on top of the ball), preparation shoulder bridge (with feet on top of the ball and performing extension and flexion of the knees), side kick (with ankle weights).
6	16	Hundred (with the feet on the floor), roll up (with TheraBand on feet), rolling like a ball, saw, preparation shoulder bridge (with feet on top of the ball), preparation shoulder bridge (with feet on top of the ball and performing extension and flexion the knees), double-leg kick.
	17 and 18	Single-leg stretches, obliques, roll over, preparation shoulder bridge performing simultaneously exercises of biceps with weight of 1 kg, hell squeeze prone (with magic circle on ankles), and spine stretch forward with pressing the magic circle with hands.
7	19	Hundred (with feet on the floor and tightening magic circle between knees), single-leg stretches, roll over, preparation shoulder bridge performing simultaneously exercises of biceps with weight of 1 kg, shoulder bridge and spine stretch forward with pressing the magic circle with hands.
	20 and 21	Side bend with knees supported, hundred (with hip and knees flexed 90 degrees), scissors with over ball in the sacral region, obliques roll (with weight of 1 kg), sing leg extension (with 1 kg ankle weights), jackknife.
8	22	Hundred (with hip and knees flexed 90 degrees), obliques roll (with weight of 1 kg), lateral flexion, single-leg extension (with 1-kg ankle weights), jackknife and hip twist with supported ribs.
	23 and 24	Roll up tightening magic circle, hundred (with hip and knees flexed 90 degrees), obliques, slow double-leg stretch, preparation shoulder bridge performing simultaneously exercises of biceps with weight of 1 kg, one-leg kick with 1-kg ankle weights, breaststroke with weight of 1 kg, side kick with 1-kg ankle weights and lateral flexion.
9	25	Roll up tightening magic circle, hundred (with hip and knees flexed 90 degrees), roll up with weight of 1 kg, slow double-leg stretch, roll over, preparation shoulder bridge performing simultaneously exercises of biceps with weight of 2 kg, one-leg kick with 1-kg ankle weights, side kick with 1-kg ankle weights and lateral flexion.
	26 and 27	Hundred (with hip and knees flexed 90 degrees and magic circle on our ankles), double-leg stretch, open-leg rocker, scissors in air, teaser (with feet flat on the floor), seal, preparation shoulder bridge with feet on top of the ball and performing simultaneously exercises of biceps with weight of 1 kg and spine stretch forward.
10	28	Hundred (with hip and knees flexed 90 degrees and magic circle on ankles), double-leg stretch, scissors in air, teaser (with feet flat on the floor) swimming, hip twist (with the ball between the ankles performing knee flexion and extension), side-kick kneeling, preparation shoulder bridge with feet on top of the ball and performing simultaneously exercises of biceps with weight of 1 kg, twist with knees on the floor, spine stretch forward.
	29 and 30	Hundred, side bend, obliques roll with weight of 1 kg, side bend, spine twist, swimming with weight of 1 kg, top-leg abduction with 1-kg ankle weights, top-leg circles with 1-kg ankle weights.
11	31	Hundred, side bend, scissors with over ball in sacral region, side bend, spine twist, swimming with weight of 1 kg, top-leg abduction with 1-kg ankle weights, top-leg circles with 1-kg ankle weights.
	32 and 33	Half-roll back, roll up, obliques, bicycle in air, teaser (with feet flat on the floor), side-kick kneeling with 1-kg ankle weights, one-leg circle with 1-kg ankle weights, staggered legs with 1-kg ankle weights, both legs together with 1-kg ankle weights and lateral flexion.
12	34	Shell stretch, half-roll back, roll up, obliques, teaser (with feet flat on the floor), one-leg circle 1-kg ankle weights, staggered legs 1-kg ankle weights both, legs together with 1-kg ankle weights and lateral flexion.
	35 and 36	Scissors in air, hundred (with magic circle on our ankles), single-leg stretch, teaser (with feet flat on the floor), rolling like a ball, swan dive (with hands supported without elevation of lower limbs), preparation shoulder (performing simultaneously exercises of biceps with weight of 1 kg), shoulder bridge and side kick with 1-kg ankle weights.
13	37	Teaser (with feet flat on the floor), hundred, double-leg stretches, open-leg rocker, swimming, side-kick kneeling, preparation shoulder bridge performing simultaneously exercises of biceps with weight of 1 kg, one-leg circle with 1-kg ankle weights, staggered legs with 1-kg ankle weights.
	38 and 39	Hundred, scissors with over ball in the sacral region, obliques roll (with weight of 1 kg), swimming, lateral flexion, single-leg extension with 1-kg ankle weights, side kick with 1-kg ankle weights, shoulder bridge.
14	40	Hundred, single-leg stretches, obliques, roll over, preparation shoulder bridge performing simultaneously exercises of biceps with weight of 1 kg, shoulder bridge, hell squeeze prone (with magic circle on our ankles), spine stretch forward (with hands on top of the magic circle performing a pressure), and swimming.
	41 and 42	Half-roll back, roll up, obliques, rolling like a ball, bicycle in air, one-leg circle with 1-kg ankle weights, staggered legs with 1-kg ankle weights, both legs together with 1-kg ankle weights and shoulder bridge.
15	43	Hundred, roll up, slow double-leg stretch, double-leg stretch, breaststroke, saw, preparation shoulder bridge (with feet on top of the ball), preparation shoulder bridge (with the feet on the ball performing extension and flexion of the knees), and double-leg kick with 1-kg ankle weights.
	44 and 45	Hundred, side bend, scissors with over ball in the sacral region, obliques roll with weight of 1 kg, preparation shoulder bridge with the feet on the ball performing simultaneously exercises of biceps with weight of 1 kg, top-leg abduction with 1-kg ankle weights, and top-leg circles with 1-kg ankle weights.
16	46	Scissors in air, teaser (with feet flat on the floor), hundred (with magic circle on our ankles), single-leg stretch, bicycle in air, rolling like a ball, swan dive with the hands supported without elevation of lower limbs, one-leg circle with 1-kg ankle weights, staggered legs with 1-kg ankle weights, preparation shoulder bridge with the feet on the ball performing simultaneously exercises of biceps with weight of 1 kg.
	47 and 48	Hundred, double-leg stretches, breaststroke, rolling like a ball, saw, preparation shoulder bridge (with feet on top of the ball), preparation shoulder bridge (with the feet on the ball performing simultaneously exercises of biceps with weight of 1 kg), and single-leg stretch with 1-kg ankle weights.

Warmup - classes 2 to 7 - breaststroke preparation (hands by hips) and preparation abdomen; classes 8 to 22/38 to 40/43 and 47 - breaststroke preparation (hands by shoulders) and preparation abdomen; classes 23 to 37/41 and 42/44 to 46 - breaststroke preparation (hands under forehead) and preparation abdomen; class 48 - breaststroke preparation (hands by shoulders) and preparation abdomen (with over ball between the knees)

Verification of the songs’ rhythm was performed by measuring the beats per minute according to the ballroom dance protocol used in the study by Braga et al. [38]. The songs will be categorized into the following groups: slow (up to 80 bpm), medium (up to 120 bpm), and fast (up to 150 bpm). The performance score was calculated using the BPM Detector Pro application.

### Safety and intensity

To control the intensity of the Pilates methods protocol and belly dance protocol, assuring that all the patients experience the same intensity of the intervention and to promote the safety of the practice of physical activity in these patients with breast cancer, heart rate (HR) control will be performed in every session using a Polar ProTrainer 5 (Polar Electro, Bethpage, NY, USA). HR values will be checked in four moments of the class: after the beginning of the class, after the warmup and stretching, after the main stage, and at the end of the class.

The safety of the intervention will be assessed every session, according to HR and patient self-report. If participants experience an adverse event, this will be brought immediately to the attention of the researchers. Adverse events will be evaluated by the researchers, who will make the decision to stop the study early, and researchers will take responsibility and provide all care to patients included in the study.

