### Control group

Women allocated to this group will be asked to continue their routine activities during the 16-week intervention period. They will be contacted every 2 months by telephone. The intervention will be offered to this group in three meetings during the 16 weeks of the intervention. The first meeting will focus on stretching exercise to be performed at home on a regular basis, a second meeting will be about self-esteem, and the last meeting will be about prevention of lymphedema. These meetings will occur with the purpose of promoting an environment where these women can talk and share their experiences with other women with breast cancer and make sure that they also receive health education information, because they will not receive the exercise intervention in the first phase of the study. These meetings were a requirement of the Ethics Committee of CEPON, a hospital that will take part in the study in Brazil, to ensure that the control group also receives possible benefits of the study. Likewise, this strategy can improve the adherence of the control group because they will feel like a group and create social bonds.

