#### Data collection

Data will be collected using an interview format with a paper questionnaire and physical tests. The principal investigator of the study, who received previous training, will conduct a 50-min interview. The questionnaire will cover general and clinical information, quality of life, and psychological variables. The physical variables will be investigated by the specific tests. All data collection will be administered before the beginning of the intervention (baseline collection) and after the conclusion of the 16-week protocol (postintervention collection), as well as 6, 12, and 24 months after intervention (maintenance collection) (see Fig. 1). The maintenance collection will take place considering the health behavior change that the belly dance and Pilates solo intervention can promote in women with breast cancer.

For the control group, data collection will be conducted using the same paper-based questionnaire and tests applied to the intervention group, with data on general and clinical information, quality of life, and physical and psychological variables. The collection will be scheduled with the participants and will take place at the same intervals as for the experimental group, before the start of the intervention (baseline collection) and after conclusion (postintervention collection) by the same principal investigator, as well as 6, 12, and 24 months after the intervention (maintenance collection). All the data collection of intervention and control groups will occur at Santa Catarina State University.

Patients who discontinue in the intervention or control group who did not show for the meeting will be collected as well and analyzed as an intention-to-treat group. During the intervention and data collection, the researchers will collect spontaneous feedback from the patients to guarantee that the study will not have any adverse events. Data from all groups (experimental and control) will be held according to the principles of good clinical practice and the Declaration of Helsinki and will be treated with confidentiality, following the current privacy policy.

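### Adverse events are looked for at up to 48 class sessions in the exercise arms but at no stated safety enquiry in controls, so recorded events outside the scheduled outcome measures cannot be compared fairly between arms

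*Protocol article*

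**What the plan says.** Safety monitoring is described in the protocol article under Safety and intensity: "The safety of the intervention will be assessed every session, according to HR and patient self-report". The researchers evaluate any adverse event and may stop the study early on that basis.

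Sessions exist only in the two exercise arms. For Pilates, "The 16-week protocol will be implemented in 60-min Pilates solo classes three afternoons per week"; for belly dance, "The 16-week protocol will be implemented in 60-min belly dance classes three afternoons per week". In both arms each class also closes with a short discussion whose content is recorded.

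For controls, the Control group section gives two kinds of contact during the 16 weeks. One is by telephone: "They will be contacted every 2 months by telephone". The other is group meetings: "The intervention will be offered to this group in three meetings during the 16 weeks of the intervention". The meetings cover home stretching, self-esteem and lymphedema prevention. No enquiry about adverse events is attached to the calls or the meetings.

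For all patients, the Data collection section says that "the researchers will collect spontaneous feedback from the patients to guarantee that the study will not have any adverse events". The same section says that control "data collection will be conducted using the same paper-based questionnaire and tests applied to the intervention group" and that this "will take place at the same intervals as for the experimental group". Table 3, the list of study assessments, has no adverse-event row.

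**The concern.** An event has to be noticed before it can be counted. If women in the classes are observed and can report problems three times a week, while controls are seen or called about five times in 16 weeks for other purposes, more events will be recorded in the exercise arms even if the true risk is the same. Spontaneous feedback does not repair this. It applies to every arm, but it depends on an occasion to give it, and those occasions are far more frequent in the classes.

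Two things are at stake. A table of adverse events by arm could make the classes look harmful when they are not, or lead a real excess to be dismissed as closer observation. And the researchers who decide on early stopping would have no comparable background frequency for the events that only these channels pick up.

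The sentence on spontaneous feedback also misstates its purpose. Listening for feedback can detect adverse events; it cannot ensure that none occur.

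**Working it through.** **Scheduled contacts during the 16 weeks**

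- Exercise arms: 3 sessions per week × 16 weeks = 48. This agrees with the 48 sessions in the captions of Tables 1 and 2.
- Controls, calls: one every 2 months, i.e. every 52/6 = 8.67 weeks; 16 / 8.67 = 1.85, about 2.
- Controls, meetings: 3.
- Control total: about 2 + 3 = 5.
- Ratio: 48 / 5 = 9.6 to 1.

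**Sensitivity of the ratio**

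- If only one call falls within the 16 weeks: 48 / 4 = 12 to 1.
- If women attend at the 78.6% adherence that the Discussion reports for the belly dance pilot: 0.786 × 48 = 37.7 sessions; 37.7 / 5 = 7.5 to 1.
- If the postintervention interview, common to all arms, is added to both sides: 49 / 6 = 8.2 to 1.

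Social meetings and social media groups are offered to all patients and are left out of the count on both sides.

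**What unequal detection would do**

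The documents give no detection probabilities, so these are assumptions, shown as a range. Let the true risk p be the same in every arm, with detection dE in the exercise arms and dC in controls. The observed risk ratio is (p × dE) / (p × dC) = dE / dC, whatever p is. Take dE = 0.90. The counts assume p = 0.20, with 2 × 19 = 38 exercisers and 19 controls.

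| dC (assumed) | Observed risk ratio | Expected recorded, exercise | Expected recorded, control |
|---|---|---|---|
| 0.30 | 0.90/0.30 = 3.0 | 38 × 0.20 × 0.90 = 6.8 | 19 × 0.20 × 0.30 = 1.1 |
| 0.50 | 0.90/0.50 = 1.8 | 6.8 | 19 × 0.20 × 0.50 = 1.9 |
| 0.70 | 0.90/0.70 = 1.29 | 6.8 | 19 × 0.20 × 0.70 = 2.7 |

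Every ratio above 1 here arises without any true difference.

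**Which harms are affected**

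- Measured alike in all arms, so not affected: arm volume from circumferences, pain on the visual analogue scale, DASH, and the pain and arm-symptom scales of the QLQ-C30 and QLQ-BR23. Table 3 schedules these measures at baseline, postintervention and follow-up, and Data collection applies the same questionnaire and tests to controls.
- Left to the unequal channels: episodes that start and resolve between visits, and events that no outcome measures, such as falls, acute musculoskeletal injury or medical visits.

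**The case against.** **No comparative safety analysis is promised.** The hypotheses, outcomes and statistical analysis contain none, and watching women more closely where exercise is delivered is ordinary participant protection. This stands, and it limits the point to what can be read from the recorded events. It does not remove it: the researchers will evaluate those events, and a reader will compare arms if events are listed by arm.

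**The article is condensed.** The interview covers general and clinical information whose items are not reproduced, so a common adverse-event question may exist in the full protocol. This also stands: its absence cannot be asserted. But the scheme that the article does describe is session-based in two arms and spontaneous elsewhere, and that is a stated choice rather than a gap.

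**Stronger readings that the documents do not support.**

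- A reader might infer that the trial cannot tell whether arm swelling or pain comes from the classes, or that controls give no background level for them. They do, through the equal scheduled measurements listed above.
- A reader might infer that spontaneous feedback is the controls' own method. It is worded for all patients.
- A reader might turn the 9.6 to 1 contact ratio directly into a ratio of recorded events. Detection is capped by the number of events that occur, so the distortion depends on detection per event, which the documents do not give.

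**Small numbers.** Even with equal enquiry, 19 women per arm say little about rare events: with none seen in 19, the one-sided 95% upper limit is 1 − 0.05^(1/19) = 14.6%. That is true, and it means the remedy removes bias without adding precision.

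**Conclusion.** The concern holds in a limited form. As the article states it, adverse-event ascertainment differs by arm: up to 48 session-based assessments against about five control contacts with no stated safety enquiry, a ratio of 9.6 to 1 (7.5 to 12 under the variations shown). Any between-arm reading of events recorded through these channels would be biased towards more events in the exercise arms. With the assumed detection of 90% against 30% to 70%, the spurious risk ratio is 3.0 to 1.29; these detection figures are illustrative only.

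The bias is confined to transient episodes between visits and to events outside the outcome list. It leaves untouched the primary outcome and the comparisons of arm volume, pain and arm symptoms at scheduled visits. The conclusion rests on the article being an accurate summary of the full protocol on safety. It is a worthwhile, cheap improvement and not a flaw in the trial's main comparison.

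**What to change.** - Add the same short set of solicited adverse-event questions (for example falls, acute injury, new or worse arm or joint symptoms, and medical visits since the last assessment) to the existing interview at postintervention and each follow-up, in all three arms.
- Base any between-arm statement about adverse events on those answers alone.
- Report events detected at sessions separately, for the two exercise arms only, as a description of what happened in the classes.
- Reword the sentence in Data collection so that feedback is collected to detect adverse events, not to guarantee their absence.

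The cost is a few minutes added to a 50-minute interview already planned for every woman, with no extra visit or staff. The downside is recall over 16 weeks, and over as much as a year between the 12- and 24-month visits. Short-lived events will be under-reported, but the recall period is the same in each arm. According to Trial status the study was still enrolling, so the questions could be added for the assessments still to come.
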